### 2.6. Outcomes and Operational Definitions

The primary outcome of this study is treatment response, operationally defined as a clinically meaningful reduction in panic symptom severity. Responders are defined as participants who achieve a ≥40% decrease in the total score of the PDSS from baseline to each follow-up assessment (2, 6, and 12 months), while participants not meeting this criterion are classified as non-responders.

This threshold was selected based on prior evidence indicating that a 35–45% decrease on disorder-specific anxiety scales corresponds to clinically meaningful improvement and early treatment benefit [30,31]. The 40% criterion also provides adequate sensitivity for detecting within-subject improvement across multiple timepoints in longitudinal designs.

To ensure conceptual coherence with the study’s transdiagnostic framework, additional analyses will examine changes in the GAD-7, DASS-21 Anxiety subscale, and LSAS as secondary outcomes, and the consistency of responder classification across these measures will be evaluated. This multi-metric approach retains sensitivity to panic-specific reactivity while enabling comparability with broader anxiety-disorder literature.

These operational definitions allow for both categorical classification (responder vs. non-responder) and continuous modeling of symptom change, facilitating the integration of clinical, behavioral, physiological, and neuroimaging predictors across the 12-month follow-up.

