### 2.7. Sample Size and Power Considerations

This study is designed to identify predictive biomarkers of treatment response through multimodal data modeling in a prospective, observational framework. Since the primary goal is to develop prediction models rather than to test predefined hypotheses, traditional power calculations based on inferential statistics are not directly applicable.

For the cross-sectional comparison between the clinical anxiety group and the healthy control group, a medium effect size (Cohen’s d = 0.5) was assumed based on prior neuroimaging meta-analyses [32]. This yielded a minimum required sample size of 36 participants per group to achieve 80% power at a two-sided α = 0.05. Accounting for a 10% attrition rate, the control group target was set at 40 participants.

Sample size planning for predictive modeling was based on guidelines by Riley et al. [33], which recommend ensuring a sufficient number of events per predictor parameter to reduce the risk of model overfitting. Although the dataset includes numerous raw variables across clinical, behavioral, physiological, and neuroimaging domains, only a subset (~20 variables) will be used in each model following feature selection procedures. Assuming a non-response rate of 25% (the reported remission rate of 38–75% at 6 months) [34,35], at least 80 non-responders would be required to ensure four events per predictor. Accordingly, the clinical anxiety group was targeted at 145 participants to allow for a 20% dropout rate and ensure sufficient statistical power for model development.

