### 3.3. Predictive Modeling of Treatment Response

The primary objective is to develop machine-learning models that predict treatment response (≥40% PDSS reduction at 2, 6, and 12 months). Binary (responder vs. non-responder) and three-group models (healthy control, responder, non-responder) will be evaluated. Predictor features will include sociodemographic and psychiatric-history variables, clinical and psychometric scores, VR-derived behavioral indices, EEG/ECG features, 3D skeletal tracing, and neuroimaging markers. In most models, age and sex will be treated as basic covariates given their known influence on neural and behavioral measures. Lifestyle variables (e.g., education, smoking, alcohol use) and treatment-related clinical variables (medication use and psychotherapy) will be systematically recorded and incorporated either as covariates to adjust for treatment effects or as candidate predictive features, depending on the specific modeling objective and analytic context.

Predictor inclusion and feature reduction will be guided by a combination of theoretical relevance and empirical criteria. Candidate variables will undergo an initial screening based on prior literature and clinical interpretability. Dimensionality will then be reduced using data-driven feature-selection procedures, such as penalized regression methods (e.g., LASSO) or feature-importance-based ranking, with the number of retained features determined by model performance and stability rather than a predefined target. Variables exhibiting substantial multicollinearity (e.g., variance inflation factor > 5), redundancy, or consistently low contribution across cross-validation folds may be excluded prior to model fitting.

All features will be standardized, and missing values handled using multiple imputations by chained equations or similar robust approaches. Depending on data characteristics, dimensionality-reduction techniques (e.g., principal component analysis) may be applied before model fitting.

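### The 25% non-response rate in section 2.7 is a 6-month remission complement, not a rate of the PDSS endpoint, and at no rate does N = 145 give four smaller-class events per predictor

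*Protocol article*

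**What the plan says.** Section 2.7 plans the clinical anxiety group around events per predictor. It expects that "only a subset (~20 variables) will be used in each model following feature selection procedures" and concludes that "at least 80 non-responders would be required to ensure four events per predictor". The rate of those events is introduced by "Assuming a non-response rate of 25% (the reported remission rate of 38–75% at 6 months", which is the only basis offered for it. The section then states that "the clinical anxiety group was targeted at 145 participants to allow for a 20% dropout rate" and treats that number as sufficient for model development.

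The outcome to be predicted is defined in section 2.6: "Responders are defined as participants who achieve a ≥40% decrease in the total score of the PDSS from baseline to each follow-up assessment", at 2, 6 and 12 months. Everyone else is a non-responder. Section 3.3 repeats the target, which is to "predict treatment response (≥40% PDSS reduction at 2, 6, and 12 months". No section gives an expected response or non-response rate on this definition, at any visit, or relates it to remission.

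**The concern.** The planning rate belongs to a different outcome and to one visit. Remission and a 40% fall in PDSS are different events. A patient whose score falls by 40% without remitting counts as a non-remitter in the borrowed figure but as a responder in this study. The complement of a remission rate is therefore a proxy for non-response, not an estimate of it. The quoted figure is for 6 months, yet it stands behind models at 2 and 12 months as well.

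The plan also names non-responders as the events whatever the rate turns out to be. What limits a binary prediction model is the smaller of the two classes. If non-response exceeds 50%, which the quoted range allows, that class is the responders.

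At stake is the number of events the study can expect from 145 patients, and so how large a model the data can support. Section 2.7 relies on that number as its protection against overfitting.

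**Working it through.** **Inputs**
- Predictors per model: about 20 (section 2.7).
- Target events per predictor: 4 (section 2.7).
- Assumed non-response: 25%, from 6-month remission of 38–75% (section 2.7).
- Enrolment 145, dropout 20% (section 2.7).
- Outcome: PDSS fall of at least 40% at 2, 6 and 12 months (sections 2.6 and 3.3).

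**Step 1. The plan's own figures.** Required events = 20 × 4 = 80, which reproduces the stated 80. The 25% plays no part in it. The enrolment figure does not reproduce: 80 / 0.25 = 320 completers, and 320 / 0.8 = 400 enrolled, against 145 stated. Working backwards, 145 × 0.8 = 116 completers, and 80 / 116 = 69.0% non-response. That rate is not stated and lies outside the quoted range.

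**Step 2. Where the 25% comes from.** 100% − 75% = 25% and 100% − 38% = 62%. The quoted remission range implies 25–62% non-remission at 6 months. The plan uses the lower end.

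**Step 3. Expected events at N = 145.** Completers = 145 × 0.8 = 116. Smaller class = min(116 × p, 116 × (1 − p)), where p is the non-response rate. Events per predictor = smaller class / 20.

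| Non-response p | Non-responders | Responders | Smaller class | Per predictor |
|---|---|---|---|---|
| 25% | 29 | 87 | 29 (non-responders) | 1.45 |
| 50% | 58 | 58 | 58 | 2.9 |
| 62% | 72 | 44 | 44 (responders) | 2.2 |

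**Step 4. The bound.** The smaller of two classes among 116 cannot exceed 58, so events per predictor cannot exceed 58 / 20 = 2.9. At the 69.0% that would give 80 non-responders, responders number 116 − 80 = 36, or 1.8 per predictor. Even with no dropout, the smaller class of 145 is at most 72, or 3.6 per predictor. Four per predictor in the smaller class is out of reach at every rate.

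**Step 5. How far the rate moves the sample size.** For 80 non-responders with 20% dropout, N is 400 at 25%. At 62%, 80 / 0.62 gives 130 completers and N = 163. If the 80 must be the smaller class at 62%, 80 / 0.38 gives 211 completers and N = 264.

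**Step 6. Direction of the error.** If everyone who remits also meets the 40% criterion, non-response is no higher than non-remission, which would make the proxy too high. If response means meeting the criterion at all three visits, which the wording of section 2.6 allows, non-response rises. The article does not say which effect is larger.

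**The case against.** Several points on the other side are sound.

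- **The 25% is the cautious choice within the quoted range.** It gives the fewest non-responders and therefore the largest required sample. A reader might infer, because it comes from the highest remission figure, that it was picked to flatter the design. The article does not support that.
- **The required 80 does not depend on the rate.** A reader might infer that the whole event target falls with the 25%. Only the expected count, and any sample size derived from it, does.
- **The shortfall below four per predictor is not caused by the borrowed rate.** It follows from 116 completers and 20 predictors at any rate. Nor can 145 be traced to the 25%, so a better rate would not by itself explain the target. The faulty multiplication is a separate and larger problem in the same paragraph. Correcting it alone, however, would leave the wrong input in place.
- **True non-response need not be below 25%.** A reader might infer that it is, because partial improvers count as responders. That depends on figures the article does not give, and the possible all-visits reading pulls the other way.
- **Differences between visits are not shown.** A reader might infer that the rate varies several-fold across 2, 6 and 12 months. The 25–62% spread is for 6 months only and says nothing about the other visits.
- **The analysis plan softens the consequence.** Section 3.3 provides for penalised selection, with the number of retained features set by performance and stability. Sections 3.3 and 3.4 add cross-validation, calibration statistics and bootstrapping, and section 3.4 labels all analyses exploratory. The planning rate therefore does not fix the final model size.

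What remains is that section 2.7 states a rate, gives a source for a different endpoint, and claims an event count that 145 patients cannot supply in the smaller class. The exploratory label does not make that statement correct.

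**Conclusion.** The point holds in a limited form. The 25% is a remission-based proxy at 6 months and not a rate of the primary endpoint; the size and direction of its error cannot be determined from the article. Over the implied 25–62% range, 116 completers give a smaller class of 29 to 58, or 1.45 to 2.9 events per predictor for 20 variables, against the stated four. Non-responders are the limiting class only up to 50% non-response; at 62% it is the 44 responders. These figures assume 20% dropout, 20 predictors, and that non-remission can stand in for non-response for want of anything better. A non-response rate below 25% would give fewer than 29 events, but would be an assumption. The paragraph should be corrected, because the event count is its stated protection against overfitting.

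**What to change.** In section 2.7:

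1. State that the 25% is a proxy taken from 6-month remission, not a rate of a 40% PDSS reduction.
2. Define events as the smaller of the two classes.
3. For each visit model, show the expected smaller-class count and events per predictor over at least 25–62% non-response. Label any lower rate as an assumption.
4. Replace the claim that 145 patients supply 80 non-responders and four events per predictor with about 29–58 events, or 1.45–2.9 per predictor for 20 variables.
5. State, here and in section 3.3, that the candidate parameters of each visit model are capped by the smaller-class count observed at that visit.

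The cost is a rewording of one paragraph with a matching sentence in section 3.3. No extra patients are needed. The stated events-per-predictor figure becomes less favourable, and the models may have to be smaller than 20 variables.

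### Section 2.7's own inputs do not lead to 145 patients: they yield about 29 non-responders against the 80 the protocol says it needs

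*Protocol article*

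**What the plan says.** Section 2.7 bases the size of the clinical anxiety group on events per predictor. It gives these elements in sequence:

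- The number of predictors: "only a subset (~20 variables) will be used in each model following feature selection procedures".
- The event rate: "Assuming a non-response rate of 25"%, with "the reported remission rate of 38–75% at 6 months" given as its source.
- The requirement: "at least 80 non-responders would be required to ensure four events per predictor".
- The target, introduced as following from the above: "the clinical anxiety group was targeted at 145 participants to allow for a 20% dropout rate and ensure sufficient statistical power for model development".

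The abstract confirms 145 patients and 40 controls, so 145 is not a misprint confined to Section 2.7. Section 2.6 defines a non-responder as a participant without a PDSS decrease of at least 40%. Section 3.3 names the prediction of this response as the primary objective and describes feature selection "with the number of retained features determined by model performance and stability rather than a predefined target".

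**The concern.** The target is presented as the result of a calculation, but no step in the text links 80 events at a 25% event rate to 145 patients. A quarter of 145 is about 36 even before any dropout, which is less than half of 80.

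The prediction model is the primary objective, and this is the only size justification given for it. The events-per-predictor rule is also the protocol's stated protection against overfitting at the planning stage. If the figures stand, a reader or ethics committee would believe that the models rest on 80 events and four per predictor, when the plan's own assumptions give little more than a third of that.

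**Working it through.** **Inputs**, all from Section 2.7: about 20 predictors per model; 4 events per predictor; event = non-responder; 25% non-response; cited remission of 38–75%, so non-remission of 25–62%; 20% dropout; 145 enrolled.

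**1. The required events reproduce.** 20 × 4 = 80.

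**2. Forward from 80 events.** Completers = 80 / 0.25 = 320. Enrolled = 320 / (1 − 0.20) = 400. With the cruder inflation 320 × 1.20 the answer is 384. Neither is near 145.

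**3. Backward from 145.** Completers = 145 × 0.80 = 116. Non-responders = 116 × 0.25 = 29. Events per predictor = 29 / 20 = 1.45. The yield is 29 / 80 = 36% of the requirement. With no dropout at all, 145 × 0.25 = 36.

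**4. Other readings of the calculation.** Counting responders as the event at 75%: 80 / 0.75 = 107 completers, 134 enrolled (129 with the cruder inflation). Reading 80 as total completers: 80 / 0.80 = 100 enrolled (96). None gives 145.

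**5. The range of non-response among 116 completers.** Section 2.7 counts non-responders as events. A binary model is limited by whichever outcome class is smaller, so both are shown.

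| Non-response | Non-responders | Per predictor (20) | Smaller class |
|---|---|---|---|
| 25% | 29 | 1.45 | 29 |
| 38% | 44 | 2.2 | 44 |
| 50% | 58 | 2.9 | 58 |
| 62% | 72 | 3.6 | 44 |

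On the plan's definition the range is 29 to 72. The smaller class runs from 29 to 58.

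**6. What would make 145 work.** After dropout: 80 / 116 = 69% non-response, above the 62% upper end. With all 145 contributing an outcome: 80 / 145 = 55%, and at 62% there would be 145 × 0.62 = 90. The second case lies inside the cited range but needs both stated assumptions to be set aside.

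**7. Predictors supported at four events each.** 29 / 4 = 7.25, so about 7. For 44 and 58 events: 44 / 4 = 11 and 58 / 4 = 14.5, so 11 to 14.

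**8. Precision of an AUC.** The documents give no expected AUC, so every value here is an assumption. Hanley–McNeil variance: [A(1 − A) + (n₁ − 1)(Q₁ − A²) + (n₂ − 1)(Q₂ − A²)] / (n₁n₂), with Q₁ = A/(2 − A), Q₂ = 2A²/(1 + A), n₁ = 29 and n₂ = 116 − 29 = 87. At A = 0.75, Q₁ = 0.600 and Q₂ = 0.643; the SE is 0.057 and the 95% half-width is 1.96 × 0.057 = 0.11. The half-width is about 0.12 at A = 0.60 and 0.08 at A = 0.90. With 58 in each class and A = 0.75 it is about 0.09.

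**The case against.** The best defence is that the 25% may be pessimistic. It is the low end of non-remission, and it equates non-remission with failure to reach a 40% PDSS reduction, so the true event rate is uncertain. Sections 3.3 and 3.4 also allow multiple imputation. If all 145 were analysed and non-response were 55–62%, there would be 80 to 90 non-responders. This part stands: it would be too strong to say that no rate in the cited range could ever produce 80. It does not repair Section 2.7, which states 25% and budgets for 20% dropout.

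A second defence is that Section 3.4 calls all analyses exploratory, and that Sections 3.3 and 3.4 provide for penalised regression, k-fold or nested cross-validation, calibration statistics and 1000 bootstrap iterations. A reader might infer from 1.45 events per predictor that the models are bound to overfit badly. The documents do not support that: the amount of overfitting was not computed, and it depends on the algorithm, the penalty and the validation used. These safeguards do not create events, however, and an exploratory label does not make a stated figure correct.

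Third, the predictor count in Section 2.7 is approximate and refers to variables left after selection. The absence of a predefined number in Section 3.3 is therefore a tension between the two sections, secondary to the arithmetic, which fails without it.

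**Conclusion.** The step from 80 events to 145 patients is wrong as written. The requirement of 80, the 25% event rate, the 20% dropout and the target of 145 cannot all stand together, and no other section supplies a missing link. At the stated assumptions the shortfall is 51 events (80 − 29). After the planned dropout it remains at every non-response rate in the cited range, although it narrows to about 8 (80 − 72) at 62%. The sufficiency claim attached to 145 is therefore unsupported.

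This rests only on the protocol's own inputs and on taking dropout as loss of the outcome. A reader might go further and conclude that 145 patients are too few for the study, or that 400 must be enrolled. The documents do not support that either: 400 is only what the present wording implies, and a smaller or differently justified model at 145 is a legitimate plan.

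**What to change.** Correct Section 2.7 and keep 145:

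1. State that 145 enrolled with 20% dropout gives 116 completers and, at 25% non-response, about 29 non-responders. Give the range of 29 to 72 across the implied 25–62%, and note that the smaller outcome class is 29 to 58.
2. Delete the claim that 145 delivers 80 events, four events per predictor or sufficient statistical power.
3. Reconcile the predictor count in Section 2.7 with Section 3.3. If the four-per-predictor rule is kept, say that 29 events support about 7 predictor parameters, and 44 to 58 events support 11 to 14.
4. If a precision statement replaces the power claim, label the AUC as assumed and give a range: about ±0.11 at 0.75 with 29 against 87, and ±0.08 to ±0.12 for AUCs from 0.90 to 0.60.

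The sponsor may also fix a cap on parameters in Section 3.3, or make more use of the continuous symptom-change model already foreseen in Section 2.6, which draws on all completers. Both are design choices and not required corrections. A parameter cap is hard to define for random forests or boosting, and it does not limit selection from a large candidate set.

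The required changes cost some rewording and no extra patients. The price is a less favourable justification of the sample size.

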## 3. Data Analysis and Statistical Methods

### 3.1. EEG and ECG Preprocessing and Feature Extraction

EEG preprocessing will follow the principles proposed by Delorme [36], emphasizing minimal and transparent signal manipulation to preserve neural signal integrity. A single 0.5-Hz high-pass filter will be applied at data loading to prevent distortion of independent component analysis (ICA) outcomes. Automated artifact cleaning (clean_rawdata [37]) will identify and interpolate flat or low-correlation channels, and ICA (runica, maxsteps = 500, double precision) will be performed for source separation. Independent components will be classified using ICLabel [38], and non-brain components with ≥0.90 confidence will be removed. This preprocessing strategy—derived primarily from Delorme [36]—is expected to enhance reproducibility, minimize preprocessing bias, and maintain the natural covariance structure of the EEG. Additional spectral or connectivity analyses (e.g., Welch power spectra, coherence, or source-level metrics) may be applied depending on the analytic objectives.

For ECG, R-peaks will be detected using established algorithms such as the Pan–Tompkins algorithm [39] or more recent approaches including adaptive methods for wearable sensors [40] and deep learning-based techniques utilizing U-Net and LSTM architectures [41,42,43], depending on signal quality and computational requirements. Physiologically implausible beats will be excluded through automated quality assessment prior to computing HRV indices.

For spectral analysis of HRV, multiple approaches will be considered, including the traditional Welch’s method [44]; the multitaper method, which offers superior variance-bias trade-offs [45,46]; and adaptive multitaper techniques optimized for biological signals [47,48]. Standard HRV parameters (standard deviation of NN interval, root mean square of successive differences, low frequency, high frequency, low-to-high frequency ratio) will be computed, and may be complemented by non-linear dynamics measures (e.g., sample entropy, detrended fluctuation analysis), time–frequency analyses (e.g., wavelet transform, Hilbert–Huang transform), and complexity metrics in exploratory analyses to comprehensively characterize autonomic nervous system dynamics.

All EEG/ECG features will be time-locked to VR events and behavioral indices(three-dimensional positional information of skeletal-points extracted from AVATAR Studio) to enable multimodal integration with clinical and neuroimaging data.

### 3.2. Brain MRI Analysis

Preprocessing for MRI data will use standardized pipelines: fMRIPrep v24.0 for T1 and resting-state fMRI (anatomical segmentation, motion correction, spatial normalization, and smoothing at 6 mm full-width half maximum), and QSIPrep v0.21 for DWI (eddy-current correction, bias-field correction, and tensor fitting).

Structural MRI, diffusion-weighted imaging (DWI), and resting-state fMRI will be analyzed to comprehensively characterize brain structure, white matter integrity, and intrinsic functional organization associated with anxiety and treatment response. Structural MRI will yield cortical thickness and gray matter volume measures; DWI will provide white matter microstructural indices, including fractional anisotropy and mean diffusivity; and resting-state fMRI will be used to derive functional connectivity, amplitude of low-frequency fluctuations, and regional homogeneity as candidate neurobiological features for group comparisons and predictive modeling.

Group-level comparisons will be performed between (i) healthy controls and anxiety participants and (ii) responders and non-responders using general linear models with age and sex as covariates. Multiple comparisons will be adjusted using the false discovery rate. Significant neural indices will be further examined as candidate predictive features in multimodal modeling.

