The primary objective of this study is to delineate neurobehavioral biomarkers associated with treatment response in individuals with anxiety-related disorders using a transdiagnostic approach. Specifically, the present study aims to delineate patterns of neural and behavioral markers that cut across diagnostic boundaries—including panic disorder, SAD, GAD, agoraphobia, and specific phobia—thereby capturing shared pathophysiological processes relevant to therapeutic responsiveness. Healthy controls are included as a reference group to distinguish disorder-related changes from normative variability. We hypothesized that multimodal integration of VR, EEG, 3D skeletal tracking, and neuroimaging data will enable a more mechanistic and predictive understanding of anxiety and its treatment response beyond categorical diagnoses.

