### 3.4. Statistical Considerations

All analyses will be exploratory and hypothesis-generating. Normality of data distributions will be verified using the Shapiro–Wilk test and residual diagnostics. If assumptions for parametric tests are violated, appropriate transformations or non-parametric alternatives will be employed. Potential covariates (age, sex, medication status, treatment type) will be included as needed. Missing data will be handled using multiple imputation or complete-case analysis, depending on the extent and mechanism of missingness.

To ensure generalizability, model interpretability, and prevention of overfitting, we will report confidence intervals, cross-validation performance variability, and model calibration statistics where applicable. Robustness checks (e.g., bootstrapping with 1000 iterations) will be performed to confirm model stability. All analyses will be implemented in R (version 4.3.1 or later) and Python (version 3.10 or later). The analysis code will be managed using a version-controlled repository (Git), and the final software environment, including package versions, will be documented to ensure reproducibility.

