This study has several methodological and practical limitations. First, the longitudinal design is asymmetric: healthy controls are assessed twice (baseline and 12 months), whereas the anxiety group is followed three times (2, 6, and 12 months), limiting short-term trajectory comparisons. Second, ongoing medication and psychotherapy may confound treatment-response estimates, although these variables will be recorded and statistically adjusted. Third, combining multimodal data (VR, EEG, ECG, MRI) entails potential synchronization errors, variable signal quality, and data-loss risks. Standardized preprocessing and quality-control pipelines have been implemented, but residual heterogeneity may remain. Finally, practical issues such as participant burden, VR sensitivity, and attrition could affect data completeness and generalizability. Despite these constraints, the protocol emphasizes reproducibility and transparent analytic procedures to support robust, hypothesis-generating findings on neurobehavioral predictors of treatment response. In summary, this protocol outlines a longitudinal, multimodal investigation designed to identify neurobehavioral predictors of treatment response in individuals with anxiety disorders. By aligning clearly defined outcomes with standardized acquisition and analysis pipelines across behavioral, physiological, and neuroimaging domains, the study aims to generate reproducible, mechanistic insights into the processes underlying anxiety improvement. The inclusion of harmonized procedures, cross-modal synchronization, and transparent analytic workflow diagrams ensures methodological rigor and clarity, thereby facilitating future replication and data sharing within the field.

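### The responder versus non-responder neural models omit baseline PDSS and diagnosis, and no clinical-only benchmark is stated against which multimodal gain could be shown

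*Protocol article*

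**What the plan says.** Section 3.2 sets out two neural group comparisons, controls versus patients and responders versus non-responders, "using general linear models with age and sex as covariates". Those p-values have a further use: "Significant neural indices will be further examined as candidate predictive features in multimodal modeling".

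Two other places widen the covariate list. Section 3.4 states "Potential covariates (age, sex, medication status, treatment type) will be included as needed". The limitations paragraph of the Discussion says of medication and psychotherapy that they may confound, "although these variables will be recorded and statistically adjusted". Neither mentions baseline severity or diagnosis.

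Section 2.6 defines response as a reduction of at least 40% in total PDSS from baseline. Section 2.2.1 admits panic disorder, social anxiety disorder, generalized anxiety disorder, agoraphobia and specific phobia. Section 2.5.2 describes the PDSS as the measure of panic-related severity.

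The Introduction hypothesizes that multimodal integration "will enable a more mechanistic and predictive understanding of anxiety and its treatment response beyond categorical diagnoses". In section 3.3 clinical and psychometric scores enter the prediction models beside the biological features. The comparisons described there are between learning algorithms and between outcome codings: "Binary (responder vs. non-responder) and three-group models (healthy control, responder, non-responder) will be evaluated".

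**The concern.** Baseline PDSS is part of the definition of response. A patient responds when the follow-up score is at most 60% of the baseline score, so responder status is generally associated with baseline severity, even when no neural mechanism of response exists. Because the PDSS is panic-specific and the sample is not, baseline PDSS may also differ by diagnosis, and responder status with it. A neural index that reflects severity or diagnosis can therefore separate responders from non-responders while adding nothing to what the baseline questionnaire already gives. False discovery rate control does not remove this, because the problem is confounding and not multiplicity.

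The same gap recurs in the prediction work. If a multimodal model reaches a certain AUC, the plan describes no comparison showing how much of it the routine clinical variables would have reached alone. Feature-importance and SHAP analyses rank contributions within one model and do not measure the gain in performance. The stated interest in prediction beyond categorical diagnosis is left without the contrast that would show it.

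**Working it through.** The plan gives no figure on this point to reproduce. The check derives the mechanism, then sizes it under stated assumptions.

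**Inputs from the protocol article (section 2.7).** Anxiety group 145, dropout 20%, assumed non-response 25%.
- Patients with follow-up: 145 × 0.8 = 116.
- Expected non-responders: 116 × 0.25 = 29. Expected responders: 116 − 29 = 87.

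**Assumed inputs, not in the documents.** Baseline PDSS (B) mean 14, SD 5; follow-up PDSS (F) mean 5 to 8.4, SD 4.5; baseline-follow-up correlation r from 0.2 to 0.7; marker-severity correlation 0.2 to 0.5. The marker carries no information on response other than through severity.

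**Mechanism.** Response means F ≤ 0.6B, that is, D = 0.6B − F ≥ 0. Then

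Corr(B, D) = (0.6·SD_B − r·SD_F) / √(0.36·SD_B² + SD_F² − 1.2·r·SD_B·SD_F) = (3 − 4.5r) / √(29.25 − 27r).

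- r = 0.2: 2.10/4.88 = 0.43
- r = 0.3: 1.65/4.60 = 0.36
- r = 0.5: 0.75/3.97 = 0.19
- r = 0.6: 0.30/3.61 = 0.08
- r = 0.7: −0.15/3.22 = −0.05

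The association is zero at r = 3/4.5 = 0.67 and changes sign above that. This explains why the problem is clear at low r and nearly absent around 0.6 to 0.7.

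**Size by simulation (116 patients, models with age and sex, two-sided 0.05 per index).** The ranges cover the assumed follow-up means and repeat simulations. The rejection rates below are for a marker-severity correlation of 0.5, without baseline PDSS in the model.
- r = 0.2: baseline PDSS alone gives AUC about 0.70; rejection 0.30 to 0.46.
- r = 0.3: AUC about 0.65 to 0.67; rejection 0.21 to 0.34.
- r = 0.5: AUC about 0.57 to 0.59; rejection 0.08 to 0.14.
- r = 0.6: AUC about 0.54; rejection 0.04 to 0.06.
- r = 0.7: AUC about 0.48; rejection 0.04 to 0.06.

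With baseline PDSS added, rejection is 0.03 to 0.07 for r from 0.2 to 0.5. For weaker markers (correlation 0.2 to 0.3), unadjusted rejection over the same r is 0.06 to 0.19.

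**Cross-check that does not model PDSS.** With 29 versus 87 patients, an omitted variable differing by 0.3 to 0.8 SD between groups, and a marker correlated 0.2 to 0.5 with it, rejection is about 0.06 to 0.46 with age and sex only and about 0.05 once the variable is included. At correlation 0.3 and 0.5 SD it is 0.10; at correlation 0.5 and 0.5 SD it is 0.21.

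**Benchmark.** If baseline PDSS alone can give an AUC near 0.70 at r = 0.2, a multimodal AUC of that size would not by itself show any biological contribution.

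**The case against.** The strongest reply has four parts.

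- **Exploratory status.** Section 3.4 declares all analyses exploratory, and section 2.7 says the aim is to develop models and not to test predefined hypotheses. A reader might infer that the study's hypothesis goes untested. That reads a broad aim as a formal test. What stands is narrower: the gain over clinical information cannot be shown from the comparisons described.
- **Clinical scores are in the models.** In section 3.3 a severity proxy competes with severity itself, and penalization or redundancy screening may remove it. This limits the risk in the prediction models. It does not reach the univariate comparisons in section 3.2, and the redundancy rule does not say that the clinical variable is kept over its proxy.
- **Unadjusted contrasts have a use.** Severity may lie on the pathway that a neural index reflects, so an age-and-sex profile of responders is a legitimate description. That is a reason to keep it beside the adjusted model.
- **The size is assumed.** This stands. No PDSS distribution or correlation is given, the effect fades within a plausible range of r, and the rates are per index before false discovery rate control. Confounding by diagnosis has not been quantified.

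Three stronger readings are tempting, and the document does not support them. That adjustment is for age and sex alone overlooks section 3.4 and the limitations, which allow for medication and treatment. That head motion or head size is neglected is not a fair inference: preprocessing includes "anatomical segmentation, motion correction, spatial normalization, and smoothing at 6 mm full-width half maximum", and group-level motion or intracranial-volume terms are routine detail that a condensed article may leave out. That the three-group model could conceal chance-level response prediction is largely met by the binary model planned beside it.

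**Conclusion.** The concern holds in limited form. Section 3.2 specifies a covariate set for the responder contrast that leaves out baseline PDSS, which is built into the outcome, and principal diagnosis, and the additions elsewhere do not supply them. Under the assumptions shown, an index that merely tracks severity is flagged in about 7% to 46% of unadjusted comparisons (marker-severity correlation 0.3 to 0.5, r from 0.2 to 0.5), against 3% to 7% after adjustment. At the weak end of that range, and at r of 0.6 to 0.7, the inflation is small or absent. The mechanism follows from the definition of response; its size in this study cannot be computed from the document. Separately, with only algorithms and outcome codings compared, predictive gain beyond diagnosis and severity cannot be shown. Both are worth correcting, and neither invalidates the design.

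**What to change.** - **Section 3.2:** add baseline PDSS and principal diagnosis to the responder versus non-responder models. Keep the age-and-sex model as a descriptive companion, labelled as such.
- **Section 3.3:** fit a clinical benchmark using age, sex, principal diagnosis, baseline severity scores and treatment at baseline, on the same cross-validation folds as the multimodal model. Report the multimodal-minus-benchmark AUC difference with its confidence interval.

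The cost is wording and one extra model, using baseline information already planned for collection. Baseline PDSS takes one degree of freedom and five diagnoses take four, so residual degrees of freedom fall from 116 − 4 = 112 to 112 − 5 = 107. Small diagnostic groups may need to be combined. With about 29 non-responders (145 × 0.8 × 0.25) the AUC difference will be imprecise, and the report should say so and not read a wide interval as evidence of no gain.
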